### Adverse events, seriousness, and reporting

An adverse event (AE) and serious AE will be determined and addressed per the International Council for Harmonisation of Technical Requirements for Pharmaceuticals for Human Use Guidelines for Good Clinical Practice [32].

All AEs and serious AEs will be captured on an adverse events report log. Serious AEs will be reported within 24 h of knowledge of the event to the sponsor and the IRB, commensurate with the determination of possible relation to the intervention. A written report will be submitted to the sponsor and IRB within 7 days of the initial reporting. Changes in the severity of an AE will be documented to allow an assessment of the duration of the event at each level of severity to be performed. AEs characterized as intermittent will require documentation of onset and duration of each episode. Study participants will be followed for 1 week after the final study supplement is consumed. If an AE occurs, which in the judgment of the study sponsor and investigators was directly caused by the study supplement or protocol activities, the study sponsor will pay for medical care as defined in the informed consent form.

### Confidentiality

Each participant will be given a pre-randomization number upon signature of the informed consent and will be assigned a randomization number upon randomization. These codes will be used to identify the participants throughout the study and during data collection and analyses. Source data and data generated during the visits will be collected using paper-based case report forms. All documentation, data, and all other information generated will be held in strict confidence in password-protected, encrypted computers. Data collected during the trial will be deidentified upon closure of the study. No personal information concerning the study data or participants will be released to any unauthorized third party. Once the study is completed and deidentifying information has been removed from study records, the sponsor will store the deidentified stool samples for use in future research.

### Analyses of biological samples

Saliva and stool samples will be frozen at −80 °C upon receipt. Stool samples will be shipped to the sponsor for analyses. DNA will be extracted from the stool samples for qPCR. Saliva samples will be used to measure salivary sIgA, cortisol, and alpha-amylase levels by enzyme-linked immunosorbent assay (ELISA) methods using commercial kits (detailed in Table 1).

### Statistical methods

The primary outcome will be tested using a linear model to determine if the adjusted mean response value differs between groups adjusting for baseline values. For secondary outcomes that measure the statistical difference in response between intervention groups (blood chemistries, perceived exertion, and salivary measures), a linear model will be used to determine if the mean response value differs between groups, adjusting for baseline values. Where relevant, differences between groups will be adjusted for sex as well as the corresponding baseline. For secondary outcomes that are only measured during the intervention period, the response between intervention groups (number of days sick, duration, and severity) will be tested by using a two-sample *t*-test. All analyses mentioned above will be performed with the intent-to-treat and per protocol populations. The per protocol population is defined as compliant participants who took at least 80% of the study supplement during the 6-week intervention period.

All hypotheses will be tested using two-sided tests with a type I error rate of *α* = 0.05 using the SAS v9.4, JMP Pro v14 (SAS Institute Inc., Cary, NC, USA), or SigmaPlot v14 (Systat Software, Inc.) software. For the continuous response data with models that require the normality of residuals and a homogeneous variance, the residuals will be assessed using plots of the standardized residuals in four ways: versus the predicted values, in a histogram, in a Q-Q plot versus the expected value under the assumed distribution, and in a boxplot. Should there be a failure of model assumptions then transformations will be applied, or non-parametric tests will be used where appropriate. The most common transformations used adjust for a skewness and heterogeneity in variance are the natural log, log base 10, or a square root transformation. If data are transformed for analysis, the least square means will be back-transformed for reporting and the standard errors of the back-transformed means will be estimated using the Delta method ^29^.

No imputation will be performed for missing variables where there is only a single outcome measured. Variables assessed daily but analyzed weekly (such as frequency and consistency of stool samples) will be averaged in the case of missing data. The variables assessed daily will be compared as the daily average per week.

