**Methods:**

This 9-week randomized, placebo-controlled, double-blind, parallel trial will assess the ergogenic effects of a probiotic (5 billion colony-forming units/day, for 6 weeks) in healthy, non-elite runners (*N*=32; 18–45 years). Participants will be monitored via daily and weekly questionnaires during the 2-week pre-baseline, 6-week intervention, and 1-week washout. Questionnaires will inquire about activity, muscle soreness, gastrointestinal symptoms, cold and flu symptoms, stool form and frequency, and adverse events. During the pre-baseline visit, maximal oxygen uptake (V̇O_2_ max) is assessed to set appropriate individualized workload settings for the treadmill time-to-exhaustion endurance tests. These time-to-exhaustion endurance running tests will be completed at an intensity of 85% VO_2_max at baseline and final visits. During these tests, self-perceived exercise effort will be rated via the Borg Rating of Perceived Exertion scale and finger sticks assessing capillary blood glucose and lactate concentrations will be collected every 3 min. Additional questionnaires will assess diet and motivation to exercise. Body composition will be assessed using air displacement plethysmography at the baseline and final visits. Hypotheses will be tested using two-sided tests, and a linear model and with a type I error rate of *α*=0.05. Primary and secondary outcomes will be tested by comparing results between the intervention groups, adjusting for baseline values.

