### Randomization, sequence generation, concealment, and blinding

The randomization scheme using pre-defined blocks will be generated using a random number generator by laboratory personnel unrelated to the study. Four codes will be used for the placebo and probiotic to preserve blinding in case an adverse event requires unblinding. Allocation will be done in a 1:1 ratio using sealed, opaque envelopes that will also conceal the randomization sequence. Participants will be stratified by sex and randomized on-site by trained staff into two parallel arms (*n*=16/arm) to receive either the probiotic or placebo. Participants and study personnel on-site (Principal Investigator and co-Investigators, research coordinator, and assistants) and off-site personnel involved in the study (project manager, laboratory manager, and technicians) will remain blinded throughout the trial. Upon study completion, the study sponsor will reveal which codes are paired. However, all research personnel related to the study will remain fully blinded until all data analyses are complete. Once all analyses are complete, all study personnel will meet for unblinding.

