### Primary and secondary outcomes

Primary and secondary outcomes are summarized in Table 1. The primary outcome measure is the difference in time-to-exhaustion during the endurance treadmill test (run at the HR corresponding to 85% of V̇O_2_ max) between the probiotic and placebo groups after a 6-week intervention. Changes will be adjusted for corresponding baseline time-to-exhaustion values. Longer time to exhaustion is a desired outcome for runners and offers a performance advantage in a competitive environment.

**Table 1 Tab1:** Descriptions of the study outcome measures

Outcome	Description
Primary	
Time-to-exhaustion during treadmill endurance run	During an endurance treadmill run performed at the heart rate (HR) corresponding to 85% maximal rate of oxygen consumption (V̇O_2_max), the participant will run until voluntary time to exhaustion (reflected by meeting 2 out of 3 criteria: respiratory quotient ratio (VCO_2_/VO_2_) ≥ 1.1; HR reaches a minimum of 85% of age-predicted maximal HR (220 minus age); rating of 17 on the 6 to 20 point Borg Rating of Perceived Exertion scale (BRPE).
Secondary	
Blood chemistries	Capillary blood samples will be collected before, during, and after the treadmill endurance test to determine concentrations of glucose and lactate. These metabolites will be quantified using commercial, handheld colorimetric devices (ContourNext EZ glucose meter, LactatePlus lactate meter).
Body composition	This variable will be assessed using the scale (to assess weight) and BOD POD®, a body composition measuring device that measures fat mass and lean muscle mass. Coefficients of variation are 12%, and ICC are 0.9 [20].
Borg Rating of Perceived Exertion Scale (BRPE):	Exertion is a subjective estimate of exercising intensity. This self-reported instrument assesses effort and fatigue due to physical work [21]. Ratings range from 6=no muscle effort to 20=maximal muscle effort possible, cannot work any harder.
Bristol Stool Scale (BSFS):	Is a 7-point, self-rated scale of changes in stool form (hardness, shape, water content) that corresponds to intestinal transit time (*r*=−0.65) [22]. This tool is being used to monitor responses to the intervention and is supported for use in gastrointestinal research.

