### Sample size

The sample size of 32 (*n*=16 per arm), calculated using SigmaPlot v. 14.0, was based on a difference of 2.5 min between groups and standard deviation of 2.0 min in time to exhaustion during endurance treadmill testing at the final visit, as reported previously by Huang et al. [12, 13]. Using a two-sided sample *t*-test with a significance level of 0.05, it was calculated that a study with 24 participants, 12 per arm would have an 80% power to detect the assumed difference between the intervention groups. To adjust for an assumed dropout rate of 20% the total sample size would be 30. To evenly stratify the participants by sex in even blocks, two additional participants were added, bringing the total sample size to 32. This would provide for an effect size of 0.8, which is deemed a large effect.

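### Sex stratifies the randomisation, but the primary model names only baseline and leaves sex to an undefined condition; fix sex in the model

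*Protocol article*

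**What the plan says.** Under Randomization, sequence generation, concealment, and blinding, the Protocol article states: "Participants will be stratified by sex and randomized on-site by trained staff into two parallel arms". Sex is the only stratification factor named. The Sample size section explains the step from 30 to 32: "To evenly stratify the participants by sex in even blocks, two additional participants were added, bringing the total sample size to 32".

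The primary analysis is described in three places, and none mentions sex:

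- Statistical methods, opening sentence: "The primary outcome will be tested using a linear model to determine if the adjusted mean response value differs between groups adjusting for baseline values".
- Primary and secondary outcomes: "Changes will be adjusted for corresponding baseline time-to-exhaustion values".
- Abstract, Methods: "Primary and secondary outcomes will be tested by comparing results between the intervention groups, adjusting for baseline values".

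Sex enters the analysis in one later sentence of Statistical methods: "Where relevant, differences between groups will be adjusted for sex as well as the corresponding baseline". It comes after the sentences on the primary model and on the baseline-adjusted secondary models, and before the two-sample t-tests.

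**The concern.** The design treats sex as important enough to stratify on and to enlarge the trial for, while the analysis makes it optional. Stratifying on a prognostic factor makes the arms alike on it, so the true sampling variance of the treatment difference no longer contains the between-sex component. A model without sex still counts that component as residual noise. Its standard error is then larger than it should be, and the test rejects less often than the nominal 5% under the null.

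The second issue is pre-specification. With no criterion for relevance, the text allows two primary models and so two primary p-values. The blinding arrangements do not wholly prevent a choice between them. The sponsor reveals which codes are paired at study completion, while staff stay blinded until analyses are complete. A two-sided p-value can be read from paired codes without knowing which pair is the probiotic.

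This is more than detail left to an analysis plan. The article states the covariate set and a discretionary rule, and following it to the letter can leave out the stratification factor.

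**Working it through.** **Inputs from the Sample size section.** Difference 2.5 min, SD 2.0 min, two-sided alpha 0.05, 12 per arm for 80% power, 20% dropout, 32 randomised.

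**The plan's own figure.** Standardised difference = 2.5/2.0 = 1.25. The exact two-sample t-test gives 79.6% power at 11 per arm and 83.3% at 12, so 12 is the smallest number that reaches 80%. 24/(1 - 0.20) = 30. Both figures reproduce.

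**Assumptions, not in the documents.** Partial R² of sex given baseline: 0 to 0.30. Arms are balanced within sex. For the simulation, the correlation between baseline and final time is 0.5.

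**Interval width.** With N analysed, the baseline-only model has N - 3 degrees of freedom and the model with sex has N - 4. The ratio of widths, with sex to without, is

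(t with N - 4 df / t with N - 3 df) × √(1 - R²).

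At 12 per arm the critical values are 2.0860 and 2.0796, a ratio of 1.0031. For R² = 0.10: 1.0031 × √0.90 = 0.952, so the interval is 4.8% narrower. The lost degree of freedom is repaid once R² exceeds 1 - (2.0796/2.0860)² ≈ 0.6%. At 16 per arm the break-even is about 0.3%.

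**Power at the protocol's effect.** 32 × 0.80 = 25.6, so take 26 completers, 13 per arm. Using 2.0 min as the residual SD gives no credit for baseline. The noncentrality is (1.25/√(1 - R²)) × √(13/2). Without sex it is 3.187 on 23 df (critical t 2.069), which gives 86.2% power. With sex at R² = 0.10 it is 3.359 on 22 df (critical t 2.074), which gives 89.4%.

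**Type I error.** Simulated with 40,000 trials per setting at 12 per arm.

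| Partial R² of sex | CI width change from adding sex (12/arm) | Power with sex (13/arm, 1.25 SD; 86.2% without) | Type I error, baseline only | Type I error, with sex | Type I error, smaller p of the two |
|---|---|---|---|---|---|
| 0 | +0.3% | 86.1% | 5.0% | 5.0% | 5.3% |
| 0.05 | -2.2% | 87.8% | 4.3% | 4.8% | 5.1% |
| 0.10 | -4.8% | 89.4% | 3.9% | 5.1% | 5.2% |
| 0.20 | -10.3% | 92.6% | 3.0% | 5.0% | 5.1% |
| 0.30 | -16.1% | 95.3% | 2.1% | 5.1% | 5.2% |

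At 16 per arm, always taking the smaller p-value gives 4.9% to 5.4%.

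**A smaller true effect.** At 1.6 min (0.8 SD), 12 per arm and correlation 0.5, simulated power is 55.4% without sex and 59.8% with it at R² = 0.10. At R² = 0.20 it is 55.6% and 65.0%.

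**The case against.** The strongest reply is that the conditional sentence may already cover the primary model. It follows the linear-model sentences and precedes the t-tests, so *relevant* could simply mean wherever a linear model is fitted. That reading is possible and cannot be excluded. A reader might infer that the primary model certainly omits sex; the text does not establish this. It also does not establish the opposite, and that ambiguity is what needs removing.

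Second, the gain may be small. Each participant runs at the heart rate corresponding to 85% of their own V̇O₂ max, and the model adjusts for that participant's own baseline time. Both may absorb much of any sex effect. This stands: the documents give no figure, and at R² = 0 adding sex widens the interval very slightly.

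Third, a reader might infer that the balance gained by stratifying is lost. It is not. Balance comes from the allocation and holds whatever model is fitted; only precision can be forgone.

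Fourth, a reader might infer serious inflation of type I error from having two candidate models. The simulation does not support that: even always choosing the smaller p-value gives about 5.4% at most.

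Finally, the covariate list for each model is commonly left to an analysis plan. That limits the weight of the point but does not remove it, because the article sets a discretionary rule rather than staying silent.

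**Conclusion.** The point holds as a modest defect of specification. The stratification factor is absent from every statement of the primary model and enters only under a condition with no criterion and no clear scope. If it is omitted and is prognostic beyond baseline, the analysis is conservative and less precise than the design allows, without bias. The size rests entirely on the assumed partial R²: negligible near zero, about 5% of interval width at 0.10 and about 16% at 0.30. The trial does not become underpowered on its own assumptions, since power at 1.25 SD exceeds 80% with or without sex. The case for changing the text is that it costs almost nothing, matches the analysis to the randomisation and leaves a single primary p-value.

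**What to change.** In Statistical methods, state that the primary linear model includes arm, baseline time-to-exhaustion and sex as fixed terms, and delete the *where relevant* condition. Use arm, the corresponding baseline and sex in the baseline-adjusted secondary linear models as well. Bring the Abstract and the Primary and secondary outcomes section into line. Make the change before the code pairings are revealed.

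The cost is a short text edit and one degree of freedom. At 26 completers the critical t moves from 2.069 to 2.074. No change to sample size or data collection is needed.

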### Probiotic intervention

The comparators were chosen to provide either active probiotic or inert placebo. The probiotic (5×10^9^ CFU/capsule) and corresponding placebo were provided by Lallemand Health Solutions Inc. This dosage was selected to determine probiotic efficacy in this athletic population. Placebo capsules contain the same excipients, namely ascorbic acid, magnesium stearate, and potato starch, without the probiotic. The probiotic and placebo capsules are sensorially identical (same smell, taste, and look) which allows for allocation concealment. Participants will receive all study capsules (probiotic or placebo) at the randomization visit and will be instructed to consume one capsule daily with a meal for 6 weeks. Criteria for discontinuing the intervention will be the occurrence of any clinical adverse event (AE) related to the intervention, laboratory abnormality, or other medical conditions (e.g., pregnancy) or situations such that continued participation in the study would not be in the best interest of the participant.

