The secondary outcomes, which will compare probiotic and placebo groups while adjusting for the corresponding baseline values, are as follows: (A) Borg Rating of Perceived Exertion (BRPE) [21] at peak lactate threshold during the endurance treadmill test (represents greater perceived tolerance to running workload); (B) exercise-induced changes in blood chemistry, specifically glucose concentrations and lactate threshold during the endurance treadmill test (reflects fuel use patterns during running); (C) biomarkers of stress (salivary cortisol and alpha-amylase) and biomarkers of immune activity (salivary secretory immunoglobulin A; sIgA); (D) cold/flu symptoms (severity, duration and number of episodes) as self-reported on the daily questionnaire [23]; (E) gastrointestinal function and discomfort as assessed by the weekly administration of the Gastrointestinal Symptoms Rating Scale (GSRS) [24] and (Digestion-associated Quality of Life Questionnaire (DQLQ) [25] and stool frequency and consistency (Bristol Stool Scale; BSFS) [22] as self-reported on the daily questionnaire; and (F) change in body composition (% fat, % fat-free mass, fat-free mass, fat mass, and body mass) from baseline between the probiotic and placebo groups.

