**Table 2 Tab2:**
[figure not shown]
Schedule of activities per visit

^a^A week before the randomization and the final visits

^b^Questionnaires are administered daily, starting 14 days before the randomization visit until 7 days after the end of the intervention (muscle soreness, cold-flu symptoms, stool frequency-consistency)

^c^Questionnaires are administered weekly starting 2 weeks before the Randomization visit until 1 week after the end of the intervention (GSRS, BSFS, DQLQ)

^d^Questionnaires are administered at baseline and final visits (sHEI, Fiber Screener, BREQ-3)

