#### Visit 4: Post-intervention treadmill endurance testing

The procedures described for the endurance test, completion of questionnaires, salivary-stool biomarkers, and activity tracking with the armband described above for visit 3 will be repeated during this post-intervention visit. Participants will return any unused probiotic capsules for compliance calculation. Participants will complete daily and weekly questionnaires for an additional week after visit 4.

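### Sick days and their duration are tested with no stated denominator for days observed, while the statements on when follow-up ends agree only for completers

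*Protocol article*

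**What the plan says.** **Outcome.** Primary and secondary outcomes lists "cold/flu symptoms (severity, duration and number of episodes) as self-reported on the daily questionnaire".

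**Test.** Statistical methods states that "the response between intervention groups (number of days sick, duration, and severity) will be tested" by a two-sample t-test. It treats these as outcomes measured only in the intervention period and applies the test in both the intent-to-treat and per protocol populations. No rate, offset or person-time is mentioned.

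**Missing data.** The same section does not impute single-measure outcomes. It averages variables that are collected daily but analysed by week, with stool frequency and consistency as the example, and closes by saying that daily variables are compared as a daily average per week. Neither sentence mentions sick days or episodes.

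**End of follow-up.** Three places set it:
- Table 2, footnote b: "Questionnaires are administered daily, starting 14 days before the randomization visit until 7 days after the end of the intervention".
- Visit 4: "Participants will complete daily and weekly questionnaires for an additional week after visit 4".
- Adverse events, seriousness, and reporting: "Study participants will be followed for 1 week after the final study supplement is consumed".

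**Early stopping.** The Probiotic intervention section begins its list with "Criteria for discontinuing the intervention will be the occurrence of any clinical adverse event (AE) related to the intervention". Potential risks and discomforts provides for withdrawal after a study-related complication. Sample size assumes 20% dropout.

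**The concern.** A count of sick days grows with the number of days on which sickness can be recorded. A day without a diary adds no sick day, and an episode still running when the diary ends is cut short. When everyone is observed for the same time this does no harm. When observation times differ by arm, a comparison of unadjusted counts mixes the treatment effect with the difference in observation.

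A difference by arm is possible here because the first discontinuation criterion is an adverse event related to the product. Illness or complaints may also cause diary lapses. Fewer cold/flu symptoms is part of the hypothesis in the Objectives section, so a shortfall of this kind could pass for a benefit or hide one, depending on which arm has the fewer observed days.

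**Working it through.** **Step 1. The follow-up statements side by side.** Take a runner whose last capsule is on day 14 of a planned 42.

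| Statement | Completer | Stops on day 14 |
|---|---|---|
| Adverse events section: 1 week after last capsule | 42 + 7 = day 49 | 14 + 7 = day 21 |
| Table 2, footnote b: 7 days after end of intervention | day 49 | day 21 or 49, depending on whether the individual or the planned end is meant |
| Visit 4: one more week after that visit | about day 49 | about day 49, if visit 4 is kept on schedule |

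They agree for completers only.

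**Step 2. Inputs for the size.** The protocol gives no expected sick rate and no planning figure for this outcome. From Sample size: 16 per arm and 20% dropout (the section's own inflation reproduces: 24 / 0.8 = 30, plus 2 for the sex strata = 32). Then 20% of 32 = 6.4, taken as 6 early stoppers.

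Assumptions that are not in the protocol: equal true sick rate in both arms, each stopper observed to one week after the last capsule, counts not adjusted for days observed, and various splits and stopping weeks.

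**Step 3. Formula.** With stopping at the end of week s and a window of W weeks, the observed fraction for a stopper is f = (s + 1)/W. With stopper proportions a and b in the two arms, the expected ratio of counts under no effect is

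[1 − a(1 − f)] / [1 − b(1 − f)]

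The sick rate cancels.

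**Step 4. Results for W = 6 (intervention period).**

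- 3 v 3: the ratio is 1.00 at any stopping week.
- 4 v 2, week 3: f = 4/6; (1 − 0.25 × 0.333)/(1 − 0.125 × 0.333) = 0.917/0.958 = 0.957, about 4% lower.
- 4 v 2, week 1: f = 2/6; (1 − 0.25 × 0.667)/(1 − 0.125 × 0.667) = 0.833/0.917 = 0.909, about 9% lower.
- 6 v 0, week 3: 1 − 0.375 × 0.333 = 0.875.
- 6 v 0, week 1: 1 − 0.375 × 0.667 = 0.75, 25% lower.
- Stopping at week 5: f = 1, so 1.00 for any split.

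If the post-intervention week is counted (W = 7), the unequal splits range from 0.73 (6 v 0, week 1) to 0.98 (4 v 2, week 5).

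**Step 5. Effect on the test.** Simulation of the two-sample t-test: 16 per arm, no true effect, overdispersed counts (gamma-Poisson, shape 1), assumed mean of 3 sick days in six weeks, 20,000 runs, two-sided 0.05.

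| Split, stopping week | Type I error, unadjusted counts | Type I error, per day observed |
|---|---|---|
| 3 v 3, week 3 | 0.043 | 0.045 |
| 4 v 2, week 3 | 0.048 | 0.047 |
| 6 v 0, week 3 | 0.054 | 0.044 |
| 6 v 0, week 1 | 0.089 | 0.047 |

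Dividing by days observed brings the ratio of means back to about 1.00 in every row. With arms this small, the main consequence is a shifted estimate. The error rate is clearly raised only in the last row.

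**Step 6. Per protocol set.** It requires 80% of capsules: 0.8 × 42 = 33.6. A runner stopping at week 3 has at most 21/42 = 50% and is excluded. One stopping at week 5 has 35/42 = 83% and stays, but loses no time in the six-week window.

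**The case against.** **Unadjusted counts are not spelled out.** A reader might infer that the plan compares raw totals. It never says so. The closing sentence on daily averages is unqualified, cold/flu symptoms are recorded daily, and stool is given only as an example. Read that way, missed days are already normalised. This stands as a reason to call the text ambiguous. It does not settle the matter, because the section assigns sick days a test that takes one value per runner, a weekly average yields several, and episode number and duration are not daily averages.

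**The one-week sentence concerns adverse events.** A reader might infer that early stoppers' diaries end a week after the last capsule. The sentence sits in the adverse-event section, no passage says this of diaries, and Table 2 can be read as a fixed calendar. That stands: the protocol leaves the diary end for early stoppers open rather than setting it short.

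**Bias needs imbalance.** A reader might infer that the arm with more stopping will look healthier. The protocol gives no reason to expect a particular imbalance, a balanced split gives none, and most unequal splits give little. Coordinators also monitor diaries and send a second reminder, which limits lapses. This stands, so the claim has to be conditional.

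**This is detail for the analysis plan.** The choice between a rate and an offset may be. But the protocol has already fixed the outcome and the test, and diary days that were never collected cannot be recovered by a later analysis plan.

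**Conclusion.** The point holds in conditional form. The protocol tests sick days and their duration in the intent-to-treat population without stating a denominator for days observed. It does not say whether its averaging rule covers them, and it leaves open when diaries end for early stoppers. If observation differs between arms, counts are lower in the arm observed less.

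Under the stated assumptions the shortfall is zero when stopping is balanced, about 4% to 9% for a 4 v 2 split, and at most 25% over the six-week window (27% over seven) among the scenarios examined. These sizes rest on assumed splits and stopping times, and on reading the test as applied to unadjusted counts with follow-up ending a week after the last capsule. If diaries run to the planned end for everyone, or if the averaging rule applies to sick days, the shortfall in sick days largely disappears.

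The primary outcome is untouched, and the per protocol analysis largely excludes early stoppers. Severity is not a total and does not shrink in proportion to days observed. This is an improvement worth making, not a threat to the trial's main conclusion.

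**What to change.** 1. Analyse sick days and the number of episodes per observed diary day within the existing t-test, or by a count model with log observed diary days as offset. Report observed diary days by arm.
2. State in Statistical methods whether the daily-average rule covers the cold/flu outcomes, and which window (six weeks, or seven with the post-intervention week) is counted.
3. Reconcile Table 2, the Visit 4 section and the adverse-event section so that the diary end date, counted from randomization, is the same for early stoppers and completers. This concerns data collection only; what the one-week sentence means for adverse-event follow-up is for the sponsor to clarify.

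Item 3 is also what protects episode duration, since a denominator cannot restore an episode that was cut off. A denominator also assumes that unobserved days resemble observed ones, so lapses caused by illness itself are only partly handled.

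The cost is wording in a few places and one denominator or offset. The diaries are electronic and already running; the added burden is that some early stoppers complete a few more weeks of short questionnaires.
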